The first ptES session of each patient is performed at our research centers, with direct supervision of unblinded members of our team, who are not directly involved with clinical evaluations. These members need to be unblinded once they offer consultations regarding app usage. In this initial training session, the different parts of the equipment are presented to the patients, as well as recommendations on when to interrupt the session (i.e. presence of pain or any serious discomfort). If any difficulties are detected during the initial training session, additional onsite training sessions can be scheduled. Once patients are deemed trained for ptES, all further sessions are performed without supervision at the patients’ homes, with recommendations to remain at physical rest (sitting or lying down), throughout the session, in a calm environment and concentrated on the app′s instructions. The app offers a tutorial on how to correctly place the headset, before each individual session, and informs patients to remove the headset after session completion. The app also notifies patients when the headset needs recharging, and sets off reminders for subsequent sessions, which can be performed after a minimum interval of 24 hours. Missed sessions can be rescheduled for the upcoming weeks, with no more than 5 sessions per week.

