Patients are evaluated online on a weekly basis by the blinded members of the research staff. Moreover, all trial patients have remote access to supervision upon request by unblinded members of the team. For this purpose, we provide a mobile number for immediate contact. If medical attention is deemed necessary, due to an intercurrence or significant adverse event, an online medical appointment is performed within at most 48 hours. If needed, patients can also be referred to an onsite clinical evaluation at our research centers. Furthermore, adherence and completion of sessions are monitored online, through the study dashboard. Early unblinding and trial discontinuation before study completion are initiated by the following circumstances: (1) significant depression worsening, defined as a > 25% increase in HDRS-17 scores from baseline, during two consecutive weekly assessments; (2) development of suicidal ideation or suicide attempt; (3) development of psychotic symptoms; (4) development of (hypo) mania and/or clinically significant mixed symptoms (YMRS ≥ 8); (5) low adherence to study protocol, defined as < 75% of completed sessions, at any point during the study; (6) absence at any weekly evaluation without justification; and (7) patient consent withdrawal.

After trial completion, the endpoint assessments will be completed by blinded members of our research team. As a final step, patients and clinical evaluators will be unblinded using the study dashboard, and eligibility for the crossover and follow-up stages will be assessed. If participation in the study is terminated at the endpoint assessment, patients are referred to their original treatment facilities.

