### Statistical analysis

2.8

As we have 3 co-primary hypotheses, each co-primary hypothesis will be considered statistically significant if a two-sided p < 0.0167 (Bonferroni-corrected) is obtained. For the analysis of the coprimary outcomes, LLM will be employed, using a first order regressive covariance structure, which includes all observed variables without the need of imputing missing data. The dependent variable is score change on the HDRS-17. Independent variables are time (all observations until week 6), and group (‘double-active,’ ‘ptES-only’ and ‘double-sham’). We will test the statistical significance between the pairwise comparisons per our primary hypotheses. We will employ an intention-to-treat (ITT) approach.

For the analysis of the secondary outcomes, linear mixed-effects models will be employed analogically to the analysis for the primary outcomes. Binary outcomes (response and remission) will be modeled using mixed logistic regression at each timepoint. Improvement in other depressive domains will be evaluated using the same linear hierarchical models described.

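### Low adherence or an unjustified missed weekly evaluation ends trial participation and unblinds, with no later rating described, which does not fit the stated intention-to-treat analysis

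*Protocol article*

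**What the plan says.** Procedures (2.4) opens its list of seven triggers with "Early unblinding and trial discontinuation before study completion are initiated by the following circumstances". Five concern safety, clinical deterioration or withdrawal of consent. Two concern behaviour: criterion 5, "low adherence to study protocol, defined as < 75% of completed sessions, at any point during the study", and criterion 6, "absence at any weekly evaluation without justification". What ends is the trial for that patient, not only the study treatment.

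The same section on outcome rating: "After trial completion, the endpoint assessments will be completed by blinded members of our research team". It describes no HDRS-17 rating for a patient who has been discontinued.

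The same section on missed sessions: "Missed sessions can be rescheduled for the upcoming weeks, with no more than 5 sessions per week". Interventions (2.3) schedules five sessions a week in weeks 1 to 3 and two a week in weeks 4 to 6, 21 in all.

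Statistical analysis (2.8) states "We will employ an intention-to-treat (ITT) approach". The primary analysis is a mixed model on HDRS-17 change, "which includes all observed variables without the need of imputing missing data", with all observations up to week 6.

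**The concern.** Adherence and attendance are post-randomisation behaviour. In an unsupervised home-use trial they may depend on lack of benefit, on the burden of device and app, and on the arm. Here the protocol turns them into missing outcome data by its own rule, and no analysis plan can recover scores that were never collected.

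The estimate may therefore answer a different question from the one that the intention-to-treat label promises. Unblinding for a reason unrelated to safety also means that self-reports gathered from the patient afterwards are no longer blinded. Finally, the adherence threshold and the make-up provision may work against each other, so that patients are removed for a shortfall that the protocol lets them repair.

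**Working it through.** **1. The plan's figures.** Sample size calculation (2.7) assumes endpoint means of 20, 18 and 16 and an SD of 5. The smallest contrast is 20 − 18 = 18 − 16 = 2 points = 0.4 × 5, as stated. The 70 per arm can be neither confirmed nor refuted, because the within-patient correlation and the dropout rate are not given. This point does not depend on it.

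**2. Non-completion so far.** Overview (2.1) reports about 80 patients started and 75 completed by December 2021. That is at most 5/80 = 6.25% from all seven triggers together, and less if some were still in treatment.

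**3. Overstatement if benefit fades.** Let d be the share of active-arm patients removed and k the share of the 2-point effect that they keep. Both are assumptions. The effect of assignment is 2(1 − d) + 2dk. If removal is unrelated to outcome, the observed-data model still targets 2.0.

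| d | k | Effect of assignment | Overstatement |
|---|---|---|---|
| 6.25% | 0 | 1.875 | 2/1.875 − 1 = 7% |
| 6.25% | 0.5 | 1.94 | 3% |
| 15% | 0 | 1.70 | 2/1.70 − 1 = 18% |
| 15% | 0.5 | 1.85 | 8% |
| any | 1 | 2.00 | 0% |

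**4. Direction.** A large-sample simulation compared the observed-data estimate with the estimate obtained when week 6 is collected on everyone. It used a first-order autoregressive structure, an assumed correlation of 0.6 per two weeks, and a true on-treatment difference of −2.0.

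| Scenario (assumed) | Observed-data estimate | Effect of assignment |
|---|---|---|
| 15% leave each arm at random, effect lost | −2.0 | −1.7 |
| 15% leave each arm at random, effect kept | −2.0 | −2.0 |
| 20% active, 10% sham; poor responders leave; effect lost | −2.5 | −1.6 |
| 10% active, 20% sham; poor responders leave; effect kept | −1.5 | −2.0 |
| 15% leave each arm at random; sham leavers worsen 3 points, active leavers keep half | −2.0 | −2.3 |

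The bias is upward, nil or downward according to who leaves and what follows. The article fixes neither.

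**5. Adherence rule against make-up provision.** Suppose that the 75% is judged each week against sessions due so far. With 5 sessions due, 4 done is 80% and 3 done is 60%, so two misses in week 1 meet criterion 5. Weeks 1 to 3 already hold the cap of 5, so the first make-up slots come in week 4 (5 − 2 = 3 spare per week).

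Assume that each unsupervised session is missed independently with probability 10%. Session 1 is the supervised training session, so four are at risk in week 1. The chance of two or more misses is 1 − 0.9⁴ − 4 × 0.1 × 0.9³ = 1 − 0.6561 − 0.2916 = 5.2%. Simulating all six weeks, with every spare slot in weeks 4 to 6 used for make-ups, 9.7% of patients trip the rule, all of them by week 3. Almost none would be under 75% of the 21 sessions at the end. At a 15% miss rate, about 23% trip the rule.

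**6. Visits without a primary measurement.** Table 1 has no HDRS-17 at weeks 1 and 5. An unjustified absence at one of those visits loses no primary score in itself, yet criterion 6 ends participation.

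**The case against.** The strongest reply has four parts.

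- **Condensed article.** It never says outright that week 6 is not collected after discontinuation, and the full protocol may provide for it. This stands as a caution: non-collection is inferred from the discontinuation of the trial and from the placing of endpoint ratings after completion. It does not remove the need to say so, because the rule as printed generates the gap.
- **Mixed model.** Scores before removal enter the model (HDRS-17 is due at baseline and weeks 2, 3, 4 and 6) and inform the fit. This stands. A reader might infer that the analysis is confined to adherers. It is not: it covers randomised patients under missing-at-random. Likewise, usability is rated weekly, so most removed patients would already have given some ratings.
- **Size and direction.** A reader might infer that the trial necessarily overstates the effect, or does so by 18% or more. The documents support neither. Such figures need 15% or more removed with all benefit lost, whereas the reported counts suggest about 6% or less so far. Step 4 shows that the sign can change.
- **Denominator.** Criterion 5 does not say whether 75% refers to sessions due so far or to all 21. If it means all 21, two misses in week 1 trigger nothing. A reader might call the two passages a plain contradiction. The clash holds only under the weekly reading.

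The qualifiers also matter: one absence counts only if unjustified, and missed sessions count only below the 75% threshold.

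**Conclusion.** The concern holds in this form: two behavioural criteria end participation and unblind, no later rating is described, and the analysis is nevertheless called intention to treat. As printed, the estimate is of an effect as if removed patients had stayed, and it relies on missing-at-random.

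The likely size at the reported completion is modest: about 7% overstatement if all benefit is lost, about 3% if half is kept. It grows to 18% at an assumed 15% removed with nothing kept. Fading benefit makes upward bias plausible, but nil or reverse bias cannot be excluded. Later attrition may differ from the early count, and Limitations and challenges (3.1) itself leaves open whether it will be higher or lower than in onsite trials.

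The adherence and make-up passages are at best ambiguous. Under weekly judgement about 10% of patients would be removed at an assumed 10% miss rate. The reported counts suggest either fewer misses or a different application of the rule. Severity: should-fix.

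**What to change.** - Separate stopping of study treatment from stopping of outcome follow-up. Offer every randomised patient who has not withdrawn consent the remaining scheduled HDRS-17 ratings, at minimum week 6, by the existing blinded raters: onsite as planned, online if needed, with the mode recorded.
- Do not unblind as a routine for criteria 5 and 6 before the week-6 rating.
- Include these scores in the intention-to-treat analysis. Keep the on-treatment analysis and an analysis that departs from missing-at-random as sensitivity analyses.
- Reconcile the adherence criterion, including its denominator, with the make-up provision. Which criteria should stop treatment is for the clinical team.

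**Cost.** A few extra ratings. Online week-6 ratings of leavers would differ in mode from the onsite ratings of completers. The estimate may be diluted: if 70 per arm gives 80% power for 2.0 points, and leaving aside the information regained from the extra ratings, power for the effect of assignment with no benefit kept is 75% at 5% removed and 64% at 15%. Patients who have already finished under the present rule are not recovered, but those still to be enrolled are protected.

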### Digitalization

2.5

The Psylect trial has been conceived as a trial with a partial degree of digitization – i.e. although the trial involves onsite evaluations and patient training, it also makes use of online technologies to ‘improve recruitment and retention, data collection, and analytics’ [48]. We perform digital procedures to screen and recruit patients, perform weekly clinical assessments of enrolled patients (from weeks 1 to 5; baseline and endpoint assessments are performed onsite), remotely monitor adherence to the home-based study protocol, receive responses of self-administered surveys and questionnaires (through the REDCap platform). Furthermore, instructional online videos for correct positioning of the headset and Bluetooth connection to the smartphones, for the active and sham iBT interventions, are also offered online.

### Data management

2.6

Study data are collected and managed using REDCap (Research Electronic Data Capture). REDCap is ‘a secure, web-based software platform designed to support data capture for research studies, providing: 1) an intuitive interface for validated data capture; 2) audit trails for tracking data manipulation and export procedures; 3) automated export procedures for seamless data downloads to common statistical packages; and 4) procedures for data integration and interoperability with external sources [49,50]. REDCap can be installed in a variety of environments, in compliance with international standards, such as HIPAA (Health Insurance Portability and Accountability Act), CFR (Code of Federal Regulations) Title 21/Part 11, FISMA (Federal Information Security Management Act), and Brazilian data management regulations (*Lei Geral de Proteção de Dados – LGPD*).

Data will be coded according to a previously developed data dictionary. Quality of data collection will be monitored by random data quality checks for consistency (e.g. depression scores compatible in different scales) and completeness (absence or few cases of missing data).

### Sample size calculation

2.7

For Psylect, we estimated a total sample size (n) of 210 randomized patients (70 patients per arm), to achieve the ability to observe statistically significant effects, with a power of 80% (1 − β = 0.8). Dropouts were assumed to increase monotonically (Weibull) and to be equally distributed between arms. We will use 4 measurements (continuous linear change from baseline, weeks 2, 4 and endpoint), between the 3 arms (time × group interaction), in the framework of linear mixed-effects models (LMM) [51,52].

For our sample size calculations, we assumed baseline depression scores and standard deviation (SD) of 25 (±5) on the HDRS-17, distributed equally between groups, based on previous works from our group [31,32,53]. Furthermore, we considered that: (1) placebo effects in the double-sham arm will impact baseline depression scores equal to 1 effect size (ES) in SD units (ES = difference in mean change divided by SD); (2) the ‘ptES-only’ arm will have the same placebo effects present in the double-sham arm (ES = 1), plus a treatment response of ES = 0.4; and, (3) the ‘double-active’ arm will have placebo effects (ES = 1) plus a larger response of ES = 0.8. Therefore, probable endpoint scores of 20, 18 and 16 were used, for ‘double-sham,’ ‘ptES-only’ and ‘double-active,’ respectively. The effect sizes were also chosen based on the results from our previous trials and considering that tDCS and online behavioral therapies have small to moderate effect sizes.

Sample size per arm was calculated based on the smallest detectable group difference (ES tDCS vs. combination = −0.4, ES placebo vs. tDCS = −0.4). Significance levels were Bonferroni corrected for 3-way pairwise comparisons (α = 0.05/3) to control family-wise error rate, while still allowing for more anti-conservative adjustment in the final analysis [54–56].

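### The 80% power claimed in section 2.7 for the two ES 0.4 comparisons does not follow from the printed inputs; it needs a high within-patient correlation that is not stated

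*Protocol article*

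**What the plan says.** Section 2.7 (Sample size calculation) gives "a total sample size (n) of 210 randomized patients (70 patients per arm"), "with a power of 80% (1 − β = 0.8"). It states the basis for that number: "Sample size per arm was calculated based on the smallest detectable group difference (ES tDCS vs. combination = −0.4, ES placebo vs. tDCS = −0.4"). The effect size is defined as "ES = difference in mean change divided by SD". The only SD printed is 5, attached to a mean baseline HDRS-17 of 25, and the assumed endpoint means are 20, 18 and 16. An ES of 0.4 is therefore 2 points.

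The calculation is placed in a linear mixed model with four measurements (baseline, weeks 2 and 4, endpoint) and a time by group interaction. Dropout is described by shape (Weibull, monotone, equal across arms) but not by rate. On alpha: "Significance levels were Bonferroni corrected for 3-way pairwise comparisons".

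Section 2.8 (Statistical analysis) adds that "each co-primary hypothesis will be considered statistically significant if a two-sided p < 0.0167 (Bonferroni-corrected) is obtained". It names a first-order regressive covariance structure, which I read as AR(1). Neither section gives a within-patient correlation or variance components.

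**The concern.** Power, sample size, alpha, effect size, SD, means and number of visits are all printed, so a reader will expect them to fit together. Put into the usual two-sample formula they do not: that formula asks for nearly twice as many patients. The repeated measures might close the gap, but only if scores within a patient are strongly correlated.

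Two of the three co-primary hypotheses in section 2.1 rest on ES 0.4: double-active versus ptES-only, and ptES-only versus double-sham. If true power for these is nearer one half, a non-significant result could be read as evidence that iBT adds nothing, or that home ptES does not work, on the strength of an 80% figure that the trial may not have.

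**Working it through.** **Inputs.** From section 2.7: n = 70 per arm, difference 2 points, SD 5, alpha 0.05/3 = 0.0167, visits at weeks 0, 2, 4 and 6. From section 2.8: two-sided test, first-order covariance. Assumed here because not printed: the correlation (0.3 to 0.9), constant SD across visits, and dropout rising linearly to 0 to 30% by week 6.

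**1. Trying to reproduce 70 per arm at 80%.** With z(1 − 0.0167/2) = 2.394 and z(0.8) = 0.842:

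n = 2 × ((2.394 + 0.842)/0.4)² = 130.9, so 131 per arm.

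Power at 70: 0.4 × √(70/2) = 2.366; 2.366 − 2.394 = −0.028; Φ = 48.9% (47.9% with the noncentral t).

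No simple variant gives 70 at ES 0.4. One-sided 0.0167 needs 111, two-sided 0.05 needs 99, and one-sided 0.05 needs 78. The ES detectable with 80% power is 3.236 × √(2/70) = 0.55, or 2.7 points.

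**2. If 5 is the SD of change, does the four-visit model help?** Under compound symmetry, SD² of change = 2σ²(1 − ρ) = 25, so σ²(1 − ρ) = 12.5. The visit times have a sum of squares about their mean of 9 + 1 + 1 + 9 = 20. The variance of the difference in six-week slope-based change is 2 × 36 × 12.5/(20 × 70) = 0.643, SE 0.802. Then 2/0.802 − 2.394 = 0.10, and power is 54% whatever the correlation.

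**3. If 5 is the SD of scores.** Compound symmetry, each arm with its own baseline mean: variance = 2 × 36 × 25(1 − ρ)/(20 × 70) = 1.286(1 − ρ). At ρ = 0.7 the SE is 0.621; 2/0.621 − 2.394 = 0.826; power 80%. The week-3 HDRS-17 visit in Table 1 changes nothing here, because week 3 is the mean of the visit times.

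First-order structure: the four-visit slope performs almost exactly like the plain baseline-to-week-6 change, whose variance is 2 × 50(1 − ρ³)/70. At ρ = 0.5 this is 1.25, SE 1.118, power 27%. At ρ = 0.9 it is 0.387, SE 0.622, power 79%.

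The other entries come from generalised least squares for the time by group contrast. 'Common' means that the two arms share one baseline mean. The first eight result rows assume no dropout except where shown.

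| Correlation (for first-order: per 2 weeks) | Compound symmetry, free baselines | Compound symmetry, common | First-order, free baselines | First-order, common |
|---|---|---|---|---|
| 0.3 | 39% | 63% | 25% | 57% |
| 0.5 | 54% | 70% | 27% | 52% |
| 0.6 | 65% | 77% | 31% | 52% |
| 0.7 | 80% | 86% | 37% | 55% |
| 0.8 | 94% | 96% | 50% | 64% |
| 0.9 | over 99% | over 99% | 79% | 86% |
| Needed for 80%, no dropout | 0.70 | 0.64 | 0.90 | 0.88 |
| Needed for 80%, 30% dropout | 0.77 | 0.75 | 0.92 | 0.91 |

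An adjacent-visit correlation of 0.90 implies 0.90³ = 0.73 between baseline and week 6.

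**4. The ES 0.8 comparison.** 0.8 × √35 − 2.394 = 2.339, so power is 99%.

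**The case against.** The strongest reply is that the trial was not sized on a single-time-point t-test. Section 2.7 names a four-visit mixed model, and its only SD belongs to baseline scores. The placebo effect of one ES moves the mean from 25 to 20, which also scales by that SD. On this reading power depends on the correlation, and a compound-symmetry value of about 0.70 gives exactly 80% with 70 per arm. Section 2.7 also assumes equal baselines across groups, so a common-baseline model is a fair choice and lowers the requirement to about 0.64.

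This stands, and it limits the point. A reader might infer that the trial simply has 48% power, or that 80% is certainly not delivered. The article supports neither: 48% belongs to the simple comparison with 5 as the SD of change, and a high enough correlation would give 80%.

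A second reply is that an article may leave the correlation and the Weibull rate to the full protocol. That is fair, and their absence alone is not the complaint. The complaint concerns the printed claim. The printed ES definition points to 48 to 54%, and the printed covariance structure reaches 80% only at an adjacent-visit correlation of about 0.9.

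**Conclusion.** The point holds in a limited form: the stated 80% is unsupported by the printed inputs, but it is not shown to be false.

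- With 5 as the SD of change, power for each ES 0.4 comparison is about 48% by a simple comparison and 54% with four visits under compound symmetry.
- With 5 as the SD of scores and compound symmetry, power is 39 to 65% (free baselines) or 63 to 77% (common baseline) at correlations of 0.3 to 0.6. It reaches 80% only at 0.64 to 0.70.
- Under the first-order structure of section 2.8, power is 27 to 50% (free) or 52 to 64% (common) at two-week correlations of 0.5 to 0.8. It reaches 80% only at about 0.88 to 0.90.

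Dropout raises every threshold. These figures rest on assumed correlations, a constant SD of 5, reading the covariance as AR(1), and no dropout unless stated. The ES 0.8 comparison is adequately powered on any of these readings at the higher correlations, and at about 99% by the simple comparison.

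**What to change.** Recompute power for the two ES 0.4 contrasts under the analysis model of section 2.8. State beside the result the correlation (or variance components), the dropout rate, whether 5 is the SD of scores or of change, and how baseline enters the model. Then restate the power, or the difference detectable with 80% power, separately for the ES 0.4 and ES 0.8 comparisons.

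Keep the 80% claim only if the assumed adjacent-visit correlation was about 0.9, or about 0.7 if compound symmetry was used. In the latter case, reconcile that choice with the first-order structure in section 2.8.

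The cost is a rewritten power statement and probably a less favourable figure. No extra patients are needed.

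### Section 2.7 leaves an unnamed, looser multiplicity adjustment open although 2.8 fixes Bonferroni; one rule should be stated, and a closed test for three arms would be the more powerful choice

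*Protocol article*

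**What the plan says.** The three co-primary hypotheses (section 2.1) are double-active against ptES-only, double-active against double-sham, and ptES-only against double-sham. They are all the pairwise comparisons of three arms on one outcome, the change in HDRS-17.

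Section 2.8 gives the decision rule without exception: "each co-primary hypothesis will be considered statistically significant if a two-sided p < 0.0167 (Bonferroni-corrected) is obtained".

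Section 2.7 uses the same level for sizing, "Significance levels were Bonferroni corrected for 3-way pairwise comparisons (α = 0.05/3", but adds that this was done "to control family-wise error rate, while still allowing for more anti-conservative adjustment in the final analysis". It cites three references for this. The text names no alternative method and no condition for using one.

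On size, section 2.7 plans 70 patients per arm for 80% power. "Sample size per arm was calculated based on the smallest detectable group difference", which is 0.4 SD for each adjacent pair of arms, and "probable endpoint scores of 20, 18 and 16 were used" for double-sham, ptES-only and double-active, with an SD of 5.

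**The concern.** Two things are at issue.

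- **The verdict is not unique.** A primary p-value of 0.03 fails under 2.8 and might succeed under the option kept in 2.7. The added words refer to the final analysis, so they can be read as reaching beyond the sizing. The term anti-conservative also normally means an inflated type I error; less conservative is presumably what was meant.
- **Bonferroni gives away power here.** The three nulls are logically linked. If any one equality between arms is false, the other two cannot both be true. Bonferroni ignores this, and the loss falls on the two 0.4 SD comparisons that determine the sample size.

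Timing matters too. Section 2.4 has patients and clinical evaluators unblinded after the endpoint assessment, followed by a check of eligibility for the crossover and follow-up phases, which depends on arm and response (section 2.2). This reads as unblinding patient by patient. About 75 patients had completed treatment by December 2021 (section 2.1). Team members may therefore know arm and outcome for individual patients while the threshold is still open.

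**Working it through.** **Inputs from the article.** Three pairwise hypotheses; two-sided level 0.05/3; 70 per arm; 80% power; adjacent effects 0.4 SD and outer effect 0.8 SD; SD 5.

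**1. The plan's own figures.** The level reproduces: 0.05/3 = 0.0167. The 70 per arm cannot be reproduced from the stated inputs alone. For a two-sample endpoint comparison:

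n = 2(z₁₋α/₂ + z₁₋β)²/d² = 2(2.394 + 0.842)²/0.4² = 2 × 10.47/0.16 ≈ 131 per arm.

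The planned mixed model reaches about 70 only with a within-patient correlation that the article does not give, for example about 0.70 under compound symmetry without dropout. The gain is therefore shown under two assumptions: (a) the planned 80% holds under Bonferroni; (b) a simple endpoint comparison with SD 5 and no dropout.

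**2. Why the second step may use 0.05.** Let the nulls be A = B, A = C and B = C. Any two together imply the third, so only two situations can produce a false rejection:

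- All three nulls are true. An error requires the smallest p to be below 0.05/3, which has probability at most 3 × 0.05/3 = 0.05.
- Exactly one null is true. Only that one can be falsely rejected, and it is never tested at a level above 0.05.

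This is Shaffer's procedure. It rejects everything Bonferroni rejects.

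**3. Power, normal approximation.** The outer comparison (0.8 SD) nearly always opens the gate. Under (b) its power at 0.0167 is Φ(0.8√(70/2) − 2.394) = Φ(4.733 − 2.394) = 0.99. Power for an adjacent comparison in the second step is then close to Φ(δ − 1.960).

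- (a) δ = 2.394 + 0.842 = 3.236. Bonferroni 0.80; Shaffer Φ(3.236 − 1.960) = Φ(1.276) = 0.90.
- (b) δ = 0.4√(70/2) = 2.366. Bonferroni Φ(2.366 − 2.394) = 0.49; Shaffer Φ(2.366 − 1.960) = 0.66.

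In sample-size terms the ratio is (1.960 + 0.842)²/(2.394 + 0.842)² = 7.85/10.47 = 0.75. Under (a), about 53 instead of 71 per arm would give 80% per adjacent comparison.

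**4. Simulation check** (400,000 trials, three arms of 70, t-tests). For (a) the error SD was set so that Bonferroni gives about 80%: SD = 2/(3.236 × √(2/70)) = 3.66.

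| Scenario | Bonferroni | Shaffer |
|---|---|---|
| (a) each adjacent comparison | 0.795 | 0.897 |
| (a) all three significant | 0.60 | 0.79 |
| (b) each adjacent comparison | 0.48 | 0.65 |
| (b) all three significant | 0.15 | 0.36 |
| SD 3.66, only one arm differs, each true difference | 0.79 | 0.86 |
| Family-wise error, all arms equal | 0.044 | 0.044 |
| Family-wise error, two arms equal and the third far away | 0.017 | 0.050 |

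No trial had a Bonferroni rejection that Shaffer missed.

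**The case against.** The strongest reply is that the operative rule is already fixed. Section 2.8 is the analysis section and allows no exception, while the clause in 2.7 follows a past-tense account of sizing. It can be read as saying only that a trial sized at the strictest level also has enough power under a milder adjustment. That reading is fair. The cited references or a separate analysis plan, neither available here, may also name the method. What remains is that the clause speaks of the final analysis and does not match 2.8; even on the softer reading it should go.

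A reader might infer that the plan fails to control the family-wise error, or that any later loosening would destroy control. The document does not support this. Bonferroni at 0.0167 is valid. Because Shaffer rejects everything Bonferroni rejects, choosing between those two after seeing the data could not exceed Shaffer's 0.05. Harm needs a choice that extends to other methods, and since the clause names none, its size cannot be stated. Nothing shows that the sponsor intends such a choice.

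Three further points stand:

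- The trial was sized for 0.0167, so Bonferroni loses no stated power.
- Significance of all three comparisons is not a target of the plan, so those rows of the table are only illustrative.
- Shaffer is not free: it has no simple matching simultaneous confidence intervals, and adopting it now relaxes a published criterion during a trial in which allocation is becoming known patient by patient.

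**Conclusion.** Sections 2.7 and 2.8 are inconsistent about how the primary p-values will be judged, and the inconsistency should be closed. It does not make the stated rule invalid.

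Plain Bonferroni is valid but more conservative than three arms require. With family-wise error still at or below 0.05, Shaffer's procedure raises power for each 0.4 SD comparison from 80% to about 90%, provided the stated power holds under Bonferroni and the arms differ as planned. For an endpoint comparison with SD 5 and complete data the gain is from 49% to 66%; with only one arm different it is from about 80% to 86%. That there is a gain does not depend on the unreported correlation and dropout rate behind the 70 per arm, which are a separate question.

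This is a cheap improvement and not a must-fix error.

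**What to change.** 1. Delete the clause in 2.7 that leaves the final adjustment open.
2. State one procedure in both 2.7 and 2.8. Preferred wording: the smallest of the three two-sided p-values is tested at 0.05/3; if it is significant, each of the other two is tested at 0.05 (Shaffer's procedure, family-wise level 0.05). All three p-values come from the same contrast in the same model.
3. Date the change before any comparison by arm, and document that it was made without comparative data.
4. If that cannot be shown, keep 0.0167 for each comparison and make only the deletion in step 1.

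The cost is one deleted clause and about one added sentence, with no extra patients. With Shaffer, the plan should also say which confidence intervals will be reported, since intervals that match the tests are not simply available.
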